## 9.6. Subsequent Visits

### Visit 2 – Radiotherapy team visit and study consent

Once Participants have been screened, they will be invited to formally enrol into the study. This process will begin with an introductory visit with the radiotherapy team. At this point patients will receive additional counselling about the radiotherapy process and possible side effects. This visit will last approximately 1 hour. If patients are still happy to proceed with the study, then written informed consent will be obtained at this point.

### Visit 3 – Planning scans

A planning contrast computed tomography (CT) scan of the stellate ganglia in the neck, necessary for the treatment planning and radiotherapy dose calculation, will be performed. Patients will lie in a supine position. To ensure they are accurately positioned for the planning scan and subsequent treatment, they will have a plastic mask made to fit over their neck and shoulders to wear for this scan. (30 minutes)

For MR based radiotherapy, participants will also undergo an additional 0.35T MRI scan performed on the MR-Linac. To ensure they are accurately positioned for the planning scan and subsequent treatment, they will again require the same plastic mask to wear for this scan. Participants will lie in a supine position and a dedicated coil will be placed around their chest, neck and head. Standard operating procedure for MR imaging of patients with implantable cardiac devices will be adhered to. The expected MR imaging time is approximately 60

### Visits 4 to 6 – Hypofractionated radiotherapy to the stellate ganglia

Over the course of one-week, patients will undergo up to 3 fractions of hypofractionated radiotherapy targeted bilaterally to the lower half of the stellate ganglia and T1-2 paravertebral chain (60 minutes).

Prior to each fraction of radiotherapy blood samples (approximately 16 ml) will be taken to monitor plasma levels of NPY and other biomarkers. Routine blood tests (including renal function, full blood count and thyroid function) will also be checked prior to the first fraction of treatment. Blood samples will be labelled with the participants' study number and stored for analysis. All stored samples will be de-identified and will only be identified by a study specific participant number and will be destroyed after processing, unless participants have specifically consented to have their samples stored for use in future studies (10 minutes)

Before and after each fraction of radiotherapy a cardiovascular examination and neurological examination will be performed by one of the study doctors paying attention to signs of Horner's syndrome

(ptosis and pupil constriction) or upper limb sensory impairment. Cardiovascular observations including postural blood pressures and heart rate will be recorded, and an electrocardiogram will be performed. New postural hypotension defined as a symptomatic postural blood pressure drop of 20mmHg will be considered significant. (10 minutes each) If any serious treatment related adverse events are detected, then no further fractions of radiation will be delivered to that patient.

#### Visits 7 to 9 – safety visits

Over the course of 6 months post completion of hypofractionated radiotherapy, patients will be followed up to monitor for treatment related adverse events and to monitor biomarker response. This will comprise 3 further study visits at 6 weeks, 3 months and 6 months (or earlier if clinically indicated) following completion of radiotherapy.

During each study visit, blood samples will be taken (approximately 16 ml) to monitor plasma levels of NPY and other biomarkers. At the final 6-month study visit (or earlier if clinically indicated) routine blood tests will also be repeated (as detailed above).

Participants will be interviewed to assess for side effects from their radiotherapy and cardiac sympathetic denervation. Physical examinations and observations will be performed, and an electrocardiogram will be taken (as detailed above). Participants will also be asked to complete the KCCQ and a symptom questionnaire to screen for any side effects from their radiotherapy or cardiac sympathetic denervation.

At the 6 months visit a final 1.5T CMR scan will also be performed at OCMR to reassess cardiac function and stellate ganglia anatomy (as detailed above).

#### ICD interrogation and monitoring

Throughout the study duration, all patients ICDs will be monitored remotely through the pacing clinic as part of standard clinical care for these patients. Prior to patient safety visits the study team will access these records to identify any device treatments (shocks or ATP) delivered for ventricular arrhythmias and determine heart rate parameters.

Figure 3. Study flow chart

[figure not shown]

### **9.7. Sample Handling**

A total of 6 samples (total volume of no more than 100 ml) will be collected during the entire study duration. Blood samples will be stored in the research facility in OCMR until processed. All stored samples for this study will only be identified by a study specific participant number and will be destroyed after processing, unless participant has given consent for use of samples in future studies when signing the consent form. All processing of these blood samples will be performed in Oxford University Laboratories, either at the John Radcliffe Hospital, or the Department of Physiology Anatomy and Genetics and will be performed by the University Research Team. Blood samples will be transported to the lab in secure containers on dry ice by a member of the study team. Here they will be centrifuged and immediately frozen to -80 °C. NPY levels will be measured using ELISA (EZHNPY-25K, Millipore) as described previously (31, 32, 76, 77).

### **9.8. Early Discontinuation/Withdrawal of Participants**

During the course of the study a participant may choose to withdraw early from the study treatment at any time. This may happen for several reasons, including but not limited to:

- The occurrence of what the participant perceives as an intolerable AE.
- Inability to comply with study procedures
- Participant decision

Participants may choose to stop treatment and/or study assessments but may remain on study follow-up.

Participants may also withdraw their consent, meaning that they wish to withdraw from the study completely.

According to the design of the study, participants may have the following three options for withdrawal;

- 1) Participants may withdraw from active follow-up and further communication but allow the study team to continue to access their medical records and any relevant hospital data that is recorded as part of routine standard of care; i.e., Remote monitoring of their ICD.
- 2) Participants can withdraw from the study but permit data and samples obtained up until the point of withdrawal to be retained for use in the study analysis. No further data or samples would be collected after withdrawal.
- 3) Participants can withdraw completely from the study and withdraw the data and samples collected up until the point of withdrawal. The data and samples already collected would not be used in the final study analysis. A limitation to this withdrawal would be any data that has already been used as part of interim analysis, including by the independent safety committee.

In addition, the Investigator may discontinue a participant from the study treatment at any time if the Investigator considers it necessary for any reason including, but not limited to:

- Pregnancy
- Ineligibility (either arising during the study or retrospectively having been overlooked at screening)
- Significant protocol deviation
- Significant non-compliance with treatment regimen or study requirements
- Clinical decision

The type of withdrawal and reason for withdrawal will be recorded in the CRF.

Withdrawn participants will be replaced

Patients who have withdrawn from the study who also opt out of further study follow up will continue to be followed indefinitely up as part of their routine clinical care. This will include follow up under the device clinic, and where applicable by the heart failure and arrhythmia service.

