|                            | Objectives                                                                                                                          | Outcome Measures                                                                                                                                                                                                              | Timepoint(s)                                                                            |
| Primary                    | Assess the safety of radiotherapy to the stellate ganglia in patients with recurrent ventricular arrhythmia                         | Treatment related serious adverse events (SAEs) defined as any grade 3 toxicity requiring hospitalization or any grade 4 to 5 toxicity in the first 6 months as defined by the common terminology criteria for adverse events | During all radiotherapy sessions and monitoring visits up to 6 months post radiotherapy |
|                            |                                                                                                                                     | Treatment related side effects based on patient symptom questionnaires and clinical examination during study visits                                                                                                           | During all radiotherapy sessions and monitoring visits up to 6 months post radiotherapy |
| Secondary                  | Assess the feasibility of radiotherapy to modify the stellate ganglia to achieve anatomical and functional sympathetic denervation. | Physical modification of the stellate ganglia as assessed on MRI imaging                                                                                                                                                      | MRI scan at the final study visit 6 months post radiotherapy                            |
|                            |                                                                                                                                     | Haemodynamic evidence of stellate ganglia modification determined by clinical and device-based heart rate dynamics and variability                                                                                            | Monitoring visits up to 6 months post radiotherapy                                      |

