#### **11.2. Description of the Statistical Methods**

To measure our primary safety endpoint, we will measure the frequency of adverse events in the 6 months post radiotherapy. Our trial is powered to detect adverse event rates of 34% (see below)

For secondary outcome measures such as changes in circulating biomarker levels (NPY) and changes in number of device therapies following radiotherapy we will use non-parametric tests such as a Wilcoxon signed rank test to determine if changes are statistically significant.

To assess correlation between changes in biomarker levels and number of device therapies we will use a correlation matrix using non-parametric correlation tests such as Spearman rank-order correlation.

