#### **11.3. Sample Size Determination**

Considering that all patients will have failed pharmacological treatments to prevent VT, the population is expected to be at particularly high risk and SAE rates  $\leq 34\%$  (as reported for surgical CSD), and efficacy rates of 50% would be clinically acceptable. To be 80% powered to demonstrate a SAE rate not

exceeding 34% (range 9-34%) on a one sided, one sample test for proportions (alpha 0.05) would require 13 patients. Considering that all patients will have failed pharmacological treatments to prevent dangerous heart rhythms, the population is expected to be at particularly high risk of further dangerous heart rhythms. Efficacy rates of 50% would be clinically acceptable. We anticipate screening at least 16 patients to allow for a 20% drop out rate, **which has been costed in our BHF grant.**

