#### **11.7. The Level of Statistical Significance**

We are 80% powered to demonstrate a SAE rate not exceeding 34% (range 9-34%) on a one sided, one sample test for proportions (alpha 0.05).

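### Withdrawal option 3, with automatic replacement and a completers-only analysis set, can take an irradiated participant's adverse-event data out of the final safety analysis

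*Protocol*

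**What the plan says.** Section 9.8 offers three ways to withdraw. The first two keep the data already collected. Under the third, "The data and samples already collected would not be used in the final study analysis". The next sentence limits this for data already used at interim, including by the independent safety committee. The first reason listed for stopping early is "The occurrence of what the participant perceives as an intolerable AE". The section also states, without condition, "Withdrawn participants will be replaced". Section 7 repeats this and continues until 13 patients have completed the escalation.

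Section 11.4 defines one analysis population, for adverse events: those who finished the bilateral radiotherapy course. Under Sections 7 and 9.6, a participant with a serious treatment-related event receives no further fractions.

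The primary objective has two outcomes (Sections 3 and 6). One is treatment-related SAEs over 6 months. The other is "Treatment related side effects based on patient symptom questionnaires and clinical examination during study visits". Section 11.2 says of the primary endpoint that "we will measure the frequency of adverse events in the 6 months post radiotherapy". Safety reporting runs from the first fraction (Section 10).

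The committee meets after each dose level and sees all patient data before each escalation (Sections 7, 10.1, 11.5). An SAE found at a follow-up visit also triggers a review (Sections 10.1, 13.3). Section 11.1 says there is no separate SAP.

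**The concern.** In a safety study, someone who was irradiated and then harmed must stay in both the count of events and the count of people treated. Three rules, each understandable alone, work together against that. Option 3 can delete the event, replacement refills the denominator with a different person, and the completers-only population drops anyone whose course was cut short. If the wish to withdraw is linked to toxicity, the reported rate falls below the true one. With 13 participants, a single case can decide whether the rate is shown to be below 34%. The final table could also differ from what the safety committee saw.

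Later analysis cannot repair this, because what may be withdrawn is a term of consent. It has to be settled in the protocol and the consent form.

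**Working it through.** **1. The plan's own figure.** Section 11.3 says that a one-sided "one sample test for proportions (alpha 0.05) would require 13 patients", with 80% power and rates of 9% and 34%. The normal approximation is n = [(1.645·√(p0·q0) + 0.842·√(p1·q1)) / (p1 − p0)]².
- Null 9%, alternative 34%: n = 12.09, so 13. The figure reproduces.
- Null 34%, true rate 9% (the direction worded in 11.3 and 11.7): n = 16.65, so 17.

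That discrepancy is a separate matter. The present point does not depend on it and takes 13 as given.

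**2. What counts as success with 13.** The exact p-value against 34% is P(X ≤ x) for X ~ Bin(n, 0.34). The one-sided 95% upper bound is Clopper–Pearson, the 0.95 quantile of Beta(x+1, n−x).
- 1/13: p = 0.66¹³ + 13·0.34·0.66¹² = 0.0045 + 0.0302 = 0.035; upper bound 31.6%.
- 2/13: p = 0.128; upper bound 41.0%.

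So a rate below 34% is shown only with 0 or 1 SAE.

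**3. Effect of one removal.** Suppose 14 people are irradiated and 2 have an SAE. One of the two uses option 3 before any committee use and is replaced by a participant without an SAE.

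| Analysis | SAE rate | Upper 95% bound | Exact p |
|---|---|---|---|
| All irradiated | 2/14 = 14.3% | 38.5% | 0.096 |
| After removal and replacement | 1/13 = 7.7% | 31.6% | 0.035 |

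The normal approximation agrees. For 2/14, z = (0.1429 − 0.34)/√(0.34·0.66/14) = −1.56, which misses −1.645. For 1/13, z = (0.0769 − 0.34)/√(0.34·0.66/13) = −2.00, which passes it.

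**4. Effect over a range.** The documents give no frequency for option 3. The 20% drop-out allowance in 11.3 does not say which kind of withdrawal, or when. *Assumption:* a share w of SAE participants use option 3 before any committee use, nobody else does, and each is replaced. The retained rate is p(1−w)/(1−pw). At a true rate of p = 34%:

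| w | Retained rate | Chance of at most 1/13 |
|---|---|---|
| 0 | 34.0% | 3.5% |
| 0.1 | 31.7% | 5.0% |
| 0.2 | 29.2% | 7.2% |
| 0.3 | 26.5% | 10.4% |
| 0.5 | 20.5% | 22.1% |

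**5. Which events the limitation reaches.**
- *SAE at a follow-up visit:* it triggers a review, so it is probably protected.
- *SAE at a treatment visit:* the trigger names follow-up visits only, so the event is exposed until the next scheduled review. If fractions were stopped, Section 11.4 excludes the participant even without option 3.
- *Side effects short of an SAE:* they trigger no review and are exposed until a scheduled one.
- *Such side effects in the last cohort after its scheduled review:* no later review is planned, so they are exposed up to 6 months.
- *Protected data:* the text does not say whether they count in the final analysis, or whether that participant is still replaced.

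**The case against.** The strongest reply is that the limitation qualifies the very sentence that removes data, so its natural reading is that committee-reviewed data stay in. SAEs are the events most likely to reach the committee. This largely stands. A reader might infer that option 3 deletes SAE results wholesale, and the documents do not support that.

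The link from toxicity to option 3 is also only possible. In Section 9.8 an intolerable event is a reason to leave study treatment. Such a participant may remain in follow-up, and options 1 and 2 keep the collected data. So the rule *can* remove people with toxicity; it does not single them out. Nor does the bias always run downward. Removing an event-free participant moves 1/14 (7.1%, upper bound 29.7%) to 1/13 (7.7%, 31.6%).

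It is tempting to contrast 2/13 with 1/13. That overstates the change, because 14 people were treated and the proper comparator is 2/14. For the second primary outcome the protocol sets no test or threshold, so an estimate can be understated there but no formal conclusion can be reversed.

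Losses would leave a trace: the CRF records the type of and reason for withdrawal, and related and unexpected SAEs go to the ethics committee. A trace is not inclusion in the analysis, however. Finally, letting participants withdraw their data is a legitimate consent choice, and replacement fills small dose cohorts. Neither is an error alone. The weakness is their combination with a completers-only safety population.

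**Conclusion.** The point holds in limited form. Followed as written, Sections 9.8 and 11.4 can drop an irradiated participant's adverse-event data from the final safety analysis and substitute another person. The clear exposure is in side effects not yet reviewed, SAEs at treatment visits before a review, and non-SAE side effects in the last cohort after its scheduled review. Most SAEs found at follow-up are probably protected, although their place in the final analysis is not stated.

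The bias is downward when withdrawal follows an adverse event. A changed conclusion (2/14 to 1/13) requires that an SAE participant uses option 3 before any committee use, that the replacement is event-free, and that the test against 34% is the one applied. The size depends on an unknown share w. The limitation pushes w towards zero for SAEs, and at zero there is no bias. The change is worth making because it is cheap and must be in place before data are withdrawn.

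**What to change.** - **Section 9.8 and the consent form:** limit option 3 to stored samples and non-safety data. State that de-identified adverse-event data, from the first fraction to withdrawal, stay in the final safety analysis.
- **Section 11.4:** define the safety population as everyone who received at least one fraction. State that replacements add to the denominator and do not substitute. Without this, changing 9.8 alone would still leave out a participant whose course was stopped.
- **If the ethics committee requires full data withdrawal:** report the number of option 3 withdrawals by dose level, with any SAE status already known to the safety committee.

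The cost is an amendment to protocol and consent wording. The real downside is that participants lose the option to remove de-identified safety data after treatment, which the ethics committee must accept.

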### **9.9. Definition of End of Study**

The end of study is once all patient visits are complete and all samples have been analysed.

## **10. SAFETY REPORTING**

This study is primarily a safety study and is specifically powered to detect SAEs (see section 11.3). The safety reporting window will be from the first fraction of radiotherapy until completion of the 6 months study follow up. A 6 months SAE reporting window is felt to be sufficient as adverse events related to cardiac sympathetic denervation should be apparent during treatment or within days, weeks or months of completion of radiotherapy if we consider trigeminal neuralgia as a parallel (78). Indeed, over the course of 6 months we will monitor any adverse events and side-effects and the expectation is that side effects will improve rather than worsen over this time period, as is observed following surgical removal of the stellate ganglia(20)

With respect to adverse events following radiotherapy, we expect to detect any dose limiting toxicity within 6 weeks of completion of radiotherapy, which is an accepted monitoring period for dose escalation trials involving radiotherapy (79). In terms of stochastic adverse effects, in the long term, ionising radiation can also cause cancer which manifests itself after many years or decades and is an accepted side-effect of the treatment. It is not likely that we would detect such adverse events even if our reporting window was extended beyond 6 months. Indeed, our study population of patients with severe heart failure and recurrent ventricular arrhythmias has a particularly poor prognosis, even despite all current available medical therapies, with mortality rates observed in excess of 50% at 5 years(67). As such late stochastic events might never become apparent.

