### **CT scan**

A computed tomography (CT) simulation scan, necessary for the treatment planning and dose calculation, will be performed with iodine contrast and delayed enhancement. Radiation is used as part of CT scanning and MR-guided radiotherapy to the stellate ganglia.

The estimated radiation dose to the patient from the CT scan is approximately 8 mSv. The risk of fatal cancer from this procedure is approximately 1 in 10,000 and equivalent to approximately 4 years' worth of background radiation (average of 2.5 mSv per year) received in the UK.

The use of iodine contrast is routine in clinical practice and safe, but there are some associated risks including allergic reactions to contrast, and contrast induced nephropathy. CT scans will be performed at sites staffed with ALS (Advanced Life Support) trained personnel and equipped with appropriate resuscitation equipment, so that patients can be treated appropriately in the rare event of a severe contrast related allergic reaction. Patients at high risk of contrast induced nephropathy will be excluded from this study as per our pre-defined exclusion criteria (section 6.3)

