## **9.5. Baseline Assessments**

### **Visit 1 – screening visit and screening 1.5 T MRI**

Eligibility of participants will be re-checked by pre-defined inclusion/exclusion criteria (see 6.2 and 6.3 for details) by the study team and MRI safety checks will be conducted. Written informed screening consent will be obtained by GCP trained investigators or research nurses who have also been trained to obtain consent for the study and procedures and listed on the study delegation log (20 minutes).

Anthropometric measurements such as height, weight, BMI will be recorded, and routine cardiovascular examination will afford the detection of any previously undiagnosed pathology that may have implications for safety. Participants will be asked to complete the Kansas City Cardiomyopathy Questionnaire (KCCQ) so assess baseline quality of life scores. Standard 12 lead electrocardiogram will be taken, which is a highly routine test, and baseline blood tests will be taken (approximately 16ml) (10 minutes)

A 1.5 T Cardiac Magnetic Resonance (CMR) scan will be performed on a 1.5 Tesla MR scanner at the OCMR with sequences optimised to minimise device related artefact to allow us to clearly visualise the stellate ganglia and heart. Participants will lie in a supine position and a dedicated coil will be placed around their chest, neck and head. Oxford University Hospitals NHS Foundation Trust has a standard operating procedure in place (developed with the Chief Investigator) for MR imaging of patients with implantable cardiac devices and this will be adhered to. The expected magnetic resonance imaging time is less than 60 -90 minutes. There is a scheduled 5–10-minute break during scanning.

We anticipate a 20-30% screening failure so we will not proceed with formal study consent until eligibility is confirmed following screening assessment. Patients who pass screening will be invited to formally enrol into the study and will proceed as outlined below. Patients who fail screening will exit at this point.

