### **10.3. Reporting Procedures for Serious Adverse Events**

A serious adverse event (SAE) occurring to a participant will be reported to the REC that gave a favourable opinion of the study where in the opinion of the Chief Investigator the event was 'related' (resulted from administration of any of the research procedures) and 'unexpected' in relation to those procedures. Reports of related and unexpected SAEs will be submitted within 15 working days of the Chief Investigator becoming aware of the event, using the HRA report of serious adverse event form (see HRA website).

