### **10.4. Reporting Procedures for Device Related Adverse Events**

All patients in this study will have MRI conditional implantable cardiac devices as defined by the inclusion criteria. All patients' cardiac implantable devices (ICD or CRT-D devices) will be set in an MRI safe mode for the duration of the scan, in accordance with the individual manufacturer's conditions and following local clinical protocols. Furthermore, as part of the individual planning of each participant's radiotherapy, the radiation dose to their device will be considered and must be below their tolerance constraints as defined by the UK Consensus (63) and American Association of Physicists in Medicine (AAPM) guidelines (64).

However, it is still theoretically possible that a device complication could occur despite adherence to these protocols. If a device related complication occurs, we will notify the device manufacturer within 1

working day for further investigation. If the device related complications affect clinical safety of the participant, immediate appropriate clinical action will be taken, which could include admission to the cardiology ward for further assessment and treatment. If such complications amount to an SAE (as defined in 10.2) and investigators consider such complications 'related' (resulted from administration of any of the research procedures) and 'unexpected' in relation to study procedures these will also be reported to REC as outlined in section 10.3.

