#### **10.5. Follow-up of Serious Adverse Events**

In the event of an SAE, participants will remain under study follow up for the duration of the study to monitor the progress of the SAE. If deemed clinically appropriate by the investigators, and with the consent of the patient, onward clinical referral to the appropriate clinical specialty will be arranged for further investigation and treatment of symptoms. This study will monitor and report on SAE which occur within the pre-specified monitoring window period as discussed in section 10.0. Following completion of the study, all patients will return to routine clinical follow up as part of their routine clinical care. This will include follow up under the device clinic and, where applicable, by the heart failure and arrhythmia service.

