## 21. APPENDIX A: SCHEDULE OF STUDY PROCEDURES

| Procedures                     | Visits            |         |         |         |         |         |         |         |         |
|--------------------------------|-------------------|---------|---------|---------|---------|---------|---------|---------|---------|
|                                | Screening visit 1 | Visit 2 | Visit 3 | Visit 4 | Visit 5 | Visit 6 | Visit 7 | Visit 8 | Visit 9 |
| Screening consent for trial    | X                 |         |         |         |         |         |         |         |         |
| Informed consent for the trial |                   | X       |         |         |         |         |         |         |         |
| Demographics                   | X                 |         |         |         |         |         |         |         |         |
| Medical history                | X                 |         |         |         |         |         |         |         |         |
| Medication history             | X                 |         |         |         |         |         |         |         | X       |
| Physical examination           | X                 |         |         | X       | X       | X       | X       | X       | X       |
| ECG                            | X                 |         |         | X       | X       | X       | X       | X       | X       |
| Laboratory tests               | X                 |         |         | X       | X       | X       | X       | X       | X       |
| Eligibility assessment         | X                 |         |         |         |         |         |         |         |         |
| Planning scans                 |                   |         | X       |         |         |         |         |         |         |
| 1.5T MRI scan                  | X                 |         |         |         |         |         |         |         | X       |
| Radiotherapy treatment         |                   |         |         | X       | X       | X       |         |         |         |
| Adverse event assessments      |                   |         |         | X       | X       | X       | X       | X       | X       |
| Symptom questionnaire          |                   |         |         | X       | X       | X       | X       | X       | X       |

|          |   |  |  |  |  |  |  |  |   |
|----------|---|--|--|--|--|--|--|--|---|
| KCCQ -23 | X |  |  |  |  |  |  |  | X |

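### The SAE window opens at the first radiotherapy fraction, so events caused by the study's own screening and planning scans fall outside it, in conflict with Sections 10.3 and 10.4

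*Protocol*

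**What the plan says.** Section 10 of the Protocol fixes the start and end of safety reporting: "The safety reporting window will be from the first fraction of radiotherapy until completion of the 6 months study follow up". Section 10.5 makes that window operative: "This study will monitor and report on SAE which occur within the pre-specified monitoring window period as discussed in section 10.0". In Appendix A the row "Adverse event assessments" is marked at Visits 4 to 9 and left blank at Visits 1, 2 and 3. The first fraction is given at Visit 4 (Section 9.6).

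Research procedures start earlier. At Visit 1, after screening consent, "A 1.5 T Cardiac Magnetic Resonance (CMR) scan will be performed on a 1.5 Tesla MR scanner at the OCMR" (Section 9.5). At Visit 3 every enrolled participant has an iodine-contrast planning CT, and those treated on the MR platform also have a 0.35T MRI (Section 9.6). On the CT, Section 9.4.2 says that "there are some associated risks including allergic reactions to contrast, and contrast induced nephropathy".

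The reporting sections are drawn more widely. Section 10.3 treats an SAE as related if it "resulted from administration of any of the research procedures", and sends it to the ethics committee if it is also unexpected. Section 10.4 uses the same test for device complications, describes the precautions for MRI and for device dose, and accepts that "it is still theoretically possible that a device complication could occur despite adherence to these protocols". Neither section sets a time limit.

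**The concern.** Participants have an ICD and have had more than one appropriate therapy in the preceding six months. They are put through an MRI with the device in an MRI-safe mode, and later a contrast CT, solely because they are in the study. If an SAE follows one of these scans, Sections 10 and 10.5 place it outside what the study monitors and reports, while Sections 10.3 and 10.4 place it inside. Staff at the site cannot follow both.

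The protocol describes the study as primarily a safety study, and the treatment cannot be planned without these scans. An account of the safety of the approach that leaves out their serious complications is incomplete. The gap matters most for people who stop before Visit 4, since no later scheduled visit would pick up their events.

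**Working it through.** No arithmetic decides this point. The check sets the window against the visit sequence.

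| Visit | Research procedure (Sections 9.5, 9.6) | Risk named in the protocol | Adverse event assessment (Appendix A) | In the Section 10 window? |
|---|---|---|---|---|
| 1 | 1.5T MRI, device in MRI-safe mode | Device complication (10.4); gadolinium reaction where contrast is used (9.4.2) | Blank | No |
| 2 | Radiotherapy counselling, study consent | None | Blank | No |
| 3 | Contrast CT; also 0.35T MRI on the MR platform | Contrast allergy and nephropathy (9.4.2); device complication (10.4) | Blank | No |
| 4 to 6 | Radiotherapy fractions | Radiotherapy and denervation effects (9.4.1) | Marked | Yes |
| 7 to 9 | Follow-up; second 1.5T MRI at Visit 9 | As above | Marked | Yes |

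1. **Scans before the window.** CT platform: 1 screening MRI + 1 planning CT = 2. MR platform: 1 + 1 + 1 planning MRI = 3.

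2. **The rule turns on when the event occurs.** Section 10.5 refers to SAEs that occur in the window. An SAE after the planning CT that comes to light at the Visit 4 assessment still occurred before the window opened. Detection at Visit 4 therefore does not bring it in.

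3. **People who never enter the window.** There are two routes out. One is screening failure after the MRI (Section 9.5). The other is withdrawal at planning because the dose limits for the device or organs at risk cannot be met (Section 7), by which time the planning CT has been done. Sections 9.3 and 9.5 expect 20–30% screening failure. On the 16 screened patients in Sections 8.1 and 11.3, that is 16 × 0.20 = 3.2 to 16 × 0.30 = 4.8, or about 3 to 5 people. This is a ceiling for the first route if 16 are screened, because some may fail before the scan. The protocol gives no figure for the second route.

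4. **Is the start date justified elsewhere?** Section 10 argues for the end of the window: six months for denervation effects, and six weeks for dose-limiting toxicity. It gives no reason for starting at the first fraction. Nothing in the protocol extends SAE collection back to consent or to the first study procedure.

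**The case against.** The best defence is that the window fits the primary endpoint. That endpoint is treatment-related toxicity, timed from the radiotherapy sessions, and the committee's routine task is dose escalation. This stands as far as the endpoint goes: no primary count changes. It does not explain why SAEs from other research procedures should go unrecorded.

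Several stronger readings are tempting, and the documents do not support them.

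- **That most study imaging lies outside the window.** Counting only the 1.5T MRIs and planning scans gives 2 of 3 (67%) on the CT platform and 3 of 4 (75%) on the MR platform. But Section 9.4.1 adds a cone-beam CT before each TrueBeam fraction, giving 2 of 6 (33%). If the MR platform also images at each of three fractions, which is an assumption, the share is 3 of 7 (43%). The share is not the argument; the named risks of the earlier scans are.
- **That all expected screening failures will have had an MRI.** Eligibility and MRI safety are checked at Visit 1 before scanning, so some may leave without one.
- **That such events would be missed altogether.** Section 10.4 requires the manufacturer to be told of any device complication within one working day. ICDs are monitored remotely throughout the study. Renal function is checked before the first fraction. Section 12 treats participant data alike whatever the screening result. These arrangements cover part of the ground, but they are not SAE recording, and the renal check reaches only those who get to Visit 4.
- **That every contrast reaction should go to the ethics committee.** Sections 10.3 and 10.4 also require the event to be unexpected. Contrast allergy and nephropathy are named risks, so they may not qualify even under a longer window.
- **That the committee-review trigger should simply be extended to Visits 1 and 3.** Sections 10.1 and 13.3 use the Section 10.2 definition, which does not ask for relatedness, and a review suspends recruitment and radiotherapy. Widening that rule would have real consequences, and the choice belongs to the sponsor.

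**Conclusion.** The concern holds as a conflict within the protocol and a gap in SAE capture. Sections 10 and 10.5 and Appendix A agree with one another, so this is a stated rule and not a slip in one place; Sections 10.3 and 10.4 point the other way. The gap covers two scans per participant on the CT platform and three on the MR platform, and everyone who leaves after the screening MRI or the planning CT.

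The number of SAEs lost cannot be estimated, because the protocol gives no SAE rate for these procedures in this population. The conclusion rests on reading the Section 10 window as governing all SAE recording, which Section 10.5 supports. A reader might infer that the primary result is biased. It is not: the endpoint count and the sample size are unaffected. The protocol should be corrected for completeness of safety reporting.

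**What to change.** - In Sections 10 and 10.5, start SAE recording and reporting at screening consent or at the first research procedure. Leave the related-and-unexpected test for ethics committee reports in Sections 10.3 and 10.4 as it is.
- In Appendix A, mark adverse event assessment at Visits 1 and 3.
- Report procedure-related SAEs from before radiotherapy separately, and keep the first fraction as the start of the primary endpoint.
- Reconcile the committee-review trigger in Sections 10.1 and 13.3, now tied to SAEs found at follow-up visits, with the longer recording period. No particular halt rule is proposed here.

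The cost is protocol and case report form wording, a few more SAE records, and a short assessment at two visits that already exist. No visit or procedure is added.
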